### Inclusion and exclusion criteria

#### Inclusion criteria

main diagnosis: alcohol use disorder according to DSM-5patients of any gender aged 18 to 65normal vision or correctable visual impairmentsufficient ability to communicate verbally and in writingability to give fully informed consent after reviewing thorough written information

#### Exclusion criteria

withdrawal of consentsevere internal, neurological, or psychiatric comorbidities (e.g., lifetime schizophrenia, bipolar disorder, or other severe mental disorders according to ICD-10 and DSM-5, such as severe depression or PTSD within the last 12 months)Exclusion criteria for an EEG/tDCS examination (e.g. metal implants in the head, epilepsy, etc.)severe withdrawal symptoms (Revised Clinical Institute Withdrawal Assessment for Alcohol Scale, CIWA-R > 7) [76] at baseline assessmentalcohol intoxication (breath alcohol concentration > 0 ‰) at any examination time pointPharmacotherapy with psychoactive substances within the last 14 days (exceptions: clomethiazole or benzodiazepines used in withdrawal treatment, provided they were discontinued at least 3 days prior; antidepressants or anxiolytics taken at stable doses)drug or alcohol use within the last 7 days during add-on treatment period (T1-T5)for women: pregnancysuicidal tendencies or danger to others

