## Background

According to the World Health Organization, alcohol consumption leads to approximately 2.6 million deaths per year [1]. In 2019, an estimated 400 million people (7% of the population aged 15 and older) were living with an alcohol use disorder (AUD) [1, 2]. In addition, about 39.5 million people were affected by other substance use disorders (SUDs) [2], which account for approximately 9–24 of life years lost [3]. Substance use is equally widespread in the German population, thus mirroring world-wide of observations of consumption and harm. According to the 2018 Epidemiological Survey of Substance Abuse, 71.6% of respondents consumed alcohol in the past 30 days, and the 12-month prevalence of AUD was 5.9% [4]. Among other drugs, cannabis was the most common, with a 12-month prevalence of consumption of 7.1% (use disorder 1.1%), followed by amphetamines (consumption 1.2%; use disorder 0.3%) [4]. Negative consequences substance use affect not only the individual, but also our society with considerable social and economic losses. Just looking at alcohol, the US was confronted with an approximate 249 billion USD loss in 2010 [5].

Consuming a substance again after a prolonged period of abstinence is defined as a relapse in the context of a pre-existing SUD. A serious relapse is one on which the individual returns completely to previous, detrimental behavioral patterns [6]. Importantly, in individuals being treated for e.g. AUD, the approximate relapse rates range between 20–80% [7]. A relapse due to increased substance craving can be triggered by confrontation with stimuli that were previously associated with the substance [8]. Especially during protracted withdrawal, which is defined as the 4–6 weeks following last substance use, craving induced by substance-associated stimuli plays a critical role in influencing the likelihood of relapse [9]. In both regards, inhibitory control over one’s actions is vital to prevent relapse. Robust inhibitory control may help to control the compulsive drive to consume substances [10], as indicated by the sizeable percentage of patients with SUDs maintaining lifetime abstinence [11]. Recently, this observation has been translated into inhibitory control trainings as a means to improve health-related behaviors [12], such as increasing abstinent days in patients with AUD [13].

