#### Secondary: effects of tDCS as an add-on treatment in SUD

4.Anodal tDCS over the right DLPFC as an add-on treatment positively influences the treatment outcome (defined as abstinence or harm reduction) for SUD patients in comparison to stimulation over the occipital cortex, inhibition training, sham stimulation or TAU alone. Therefore, during the follow-up period (T6-T9), time to first relapse (treatment outcome: duration of abstinence) and amount of substance consumed (treatment outcome: harm reduction) is expected to be longer and less, respectively.

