### Experimental procedure

*N* = 162 SUD patients, who voluntarily enter a qualified detoxification treatment program, will be examined (inpatient or day-clinic setting) at the Department of Addictive Behaviour and Addiction Medicine at the Central Institute of Mental Health in Mannheim, Germany and the Clinic for Addiction Therapy and Withdrawal at the Psychiatrisches Zentrum Nordbaden in Wiesloch, Germany. A randomized assignment (block randomization with permuted blocks of size 12) to one of six groups will be performed. All participants will be included during their second week of hospital stay to ensure completed detoxification (at least 7 days of abstinence) and enrollment in the treatment as usual (TAU). TAU comprises an at least three weeks long therapy duration including medical and therapeutic treatment. We will follow a placebo-controlled single-blind study design, in which participants do not receive any information about electrode placement or active vs. sham condition, except in the non-tDCS groups, namely group 5 (inhibition training) and group 6 (TAU).

Four groups will receive 20-min tDCS sessions using the Sooma Duo™ device (Sooma Oy, Helsinki, Finland) over five consecutive days at an intensity of 2 mA (≈0.08 mA/cm^2^). Electrodes (25 cm^2^) will be placed using a standardized EEG cap following the 10–20 system to ensure consistent positioning across sessions [44]. The current will be ramped up from 0.3 mA to 2 mA at 0.1 mA/s, maintained for 20 min during active stimulation. Stimulation sites will differ by group:

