**Fig. 1 Fig1:**
[figure not shown]
Study design including four follow-ups over a period of 6 months

On the *first day* (T1/baseline assessment; e.g. Monday), all individuals are comprehensively informed about the goals of the proposed study and all study-related measures. Individuals will give their written informed consent and will receive a copy of the relevant study information and consent agreement. Subsequently, diagnostic interviews will be performed to assess eligibility for study participation, pre-existing conditions (mental, neurological and somatic in nature), validate the diagnoses of SUD, and assess current consumption habits. Pregnancy and drug tests will also be completed. Eligible participants will be asked to complete questionnaires and computer-based neuropsychological assessments (see Table 1). Participants will receive an EEG recording during one part of the neuropsychological assessment, namely during a modified Go/No-Go paradigm including various working memory loads [78] to assess the interaction between working memory load and response inhibition programmed in Presentation® software (Neurobehavioral Systems, Inc., Berkeley, CA, USA). At the Wiesloch study site, EEG recordings are conducted using a mobile EEG system (24 channels with active electrodes; sampling rate 1000 Hz; mBrainTrain, Belgrade, Serbia). At the Mannheim site, stationary EEG assessments are performed using BrainVision Recorder software package (32 channels with active electrodes; sampling rate 1000 Hz; Brain Products GmbH, Gilching, Germany). Two channels are occupied by the tDCS electrodes for both systems (for groups 1,2 and 4: F3 and F4; for group 3: Cz and O1). After completing all assessments, participants receive their first add-on treatment. For the first tDCS session, the tDCS study groups (groups 1 to 3) will receive a 20-min long tDCS with 0.08 mA/cm2, over the respective brain areas. The inhibition training group will perform a go-/no-go training according to Stein et al. [13] and the sham group will receive a 20 min long sham tDCS. Before and after the stimulation or training, craving will be assessed (see Table 1).

**Table 1 Tab1:** Measurements and interventions

		T1	T2-T4	T5	T6-7	T8	T9
Baseline information and medical screening	Sociodemographic data	X					
	Internistic, neurological examination	X					
	Drug/pregnancy urine screening	X		X		X	
	Menstrual cycle	X					
	Structured Clinical Interview for DSM-5	X					

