### Risks and strengths of the study

Risks regarding successful study completion primarily include dropouts and relapse. Study completion will be possible in case of relapse, to not only reduce the threshold for participants to keep in touch, but to additionally examine the aspect of harm reduction, namely reduced substance consumption in the absence of abstinence. Stepwise reimbursement is intended to support participation during the follow-up period.

The advantages of this study outweigh the risks. tDCS is a mobile, low-cost, and easy-to-administer technique, with potential for at-home use post-discharge. Devices enabling self-stimulation of the DLPFC are already available and require no specialized training. Notably, tDCS has been established as a safe, well-tolerated adjunct treatment for depression [99], and may hold promise for SUD treatment. However, more evidence is needed to support its clinical application in an addiction context. Although alcohol-withdrawing individuals may have a lower seizure threshold [100], a review of tDCS safety has not identified any serious adverse effects for conventional tDCS protocols (≤ 40 min, ≤ 4 mA, ≤ 7.2 Coulombs), even in neurologically vulnerable populations such as those with stroke or epilepsy [101].

Examining individuals with different kind of SUDs allows drawing conclusions regarding general (neuro-)biological mechanisms and treatment options for a large body of affected individuals, not only a small subgroup with a specific SUD. In addition, we will be able to investigate in a large heterogeneous sample whether there are individual factors that influence the treatment response in order to analyze whether the one-size-fits-all approach is appropriate here or whether the approach is particularly suitable for a subset of patients.

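### Two exclusion criteria can act after randomisation on substance use itself, and the breath-alcohol criterion at the 12-week visit conflicts with the statement that relapsed participants can complete the study

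*Protocol article*

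**What the plan says.** All references are to the protocol article.

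- **Exclusion criteria.** One item is "drug or alcohol use within the last 7 days during add-on treatment period (T1-T5"). Another is breath alcohol above 0 ‰, worded to apply whenever a participant is examined. The withdrawal-symptom item in the same list is tied to the baseline assessment; these two are not. The list also names withdrawal of consent, so it is not confined to screening.
- **Experimental procedure.** "All participants will be included during their second week of hospital stay to ensure completed detoxification (at least 7 days of abstinence"). Allocation uses "block randomization with permuted blocks of size 12". On day 1 (T1), "After completing all assessments, participants receive their first add-on treatment".
- **Risks and strengths of the study.** "Study completion will be possible in case of relapse, to not only reduce the threshold for participants to keep in touch", and also "to additionally examine the aspect of harm reduction, namely reduced substance consumption in the absence of abstinence".
- **Background.** "Consuming a substance again after a prolonged period of abstinence is defined as a relapse".
- **Secondary hypothesis.** The outcomes are "time to first relapse (treatment outcome: duration of abstinence) and amount of substance consumed", placed in the follow-up period T6-T9.
- **Follow-up 3.** T8, at 12 weeks, is the only on-site follow-up. It collects the Go/No-Go task with EEG, craving, relapse and consumption.

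**The concern.** An eligibility rule applied before allocation only shapes the population. The same rule applied after allocation selects on what happened under treatment. Here the trigger is drinking or drug use. It is the event behind the secondary outcomes and is closely linked to craving, a primary outcome. If people are removed for it, those who remain in each arm are no longer the groups that were randomised.

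There is also a practical problem. A participant who has relapsed and has a positive breath test at T8 meets an exclusion criterion under one section, and under another is someone the study means to keep so that harm reduction can be examined. Two sites working from this text could handle the same person differently.

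**Working it through.** **1. When the criteria act.** Seven days of abstinence are already required at inclusion, so the use criterion adds little at T1. The first session is on T1, so allocation must precede it, and T2-T5 fall after randomisation. The breath criterion has no end point. T6, T7 and T9 are telephone contacts, so in follow-up it can bite only at T8.

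**2. Comparison with the retention statement.**

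| Situation | Exclusion criteria | Risks and strengths | Conflict? |
|---|---|---|---|
| Relapsed, positive breath test at T8 | Meets a criterion | May complete | Yes |
| Relapsed, breath test negative at T8 | Breath criterion not met | May complete | No |
| Use during T2-T5 | Meets a criterion | May complete, if the statement covers the treatment period | Only on that reading |

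The Background definition of relapse would cover use in T2-T5, but the retention statement does not name a period.

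**3. Occasions for detection.** Groups 1-5 attend daily. The Experimental procedure section gives group 6 (treatment as usual) no contact at T2-T4. A rule triggered at examinations therefore has fewer chances to remove a group 6 participant during treatment.

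**4. The plan's own allowance for loss.** The Sample size section gives 25 per group (f = 0.15, power 80%, alpha 5%, within-between interaction). The number of measurements m and their correlation ρ are not stated. With m = 2 and ρ = 0.5 (assumed), λ = f²·N·m/(1−ρ) = 0.0225 × 150 × 2/0.5 = 13.5 on 5 and 144 df. This gives power 0.806, and 25 per group reproduces. Enrolling 27 allows 2/27 = 7.4% loss, or 12 of 162. The examples given are non-compliance and hardware failure. If total loss including these exclusions were 10%, 20% or 30% (assumed), 27 × (1−d) leaves 24.3, 21.6 or 18.9 per group.

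**5. Illustrations of bias (all rates assumed).**

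*(a) With a true effect.* Let relapsers score 1 SD higher on craving, with relapse p = 0.4 under active and 0.6 under control, and let a share e of relapsers be removed. The mean among those kept is p(1−e)/(1−pe).

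| e, active / control | Active | Control | Difference (SD) |
|---|---|---|---|
| 0 / 0 | 0.400 | 0.600 | 0.20 |
| 0.1 / 0.1 | 0.36/0.96 = 0.375 | 0.54/0.94 = 0.5745 | 0.1995 |
| 0.2 / 0.2 | 0.32/0.92 = 0.348 | 0.48/0.88 = 0.545 | 0.198 |
| 0.5 / 0.5 | 0.20/0.80 = 0.250 | 0.30/0.70 = 0.429 | 0.18 |
| 0.3 / 0.1 | 0.28/0.88 = 0.318 | 0.54/0.94 = 0.574 | 0.26 |
| 0.1 / 0.3 | 0.36/0.96 = 0.375 | 0.42/0.82 = 0.512 | 0.14 |

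*(b) With no true effect.* Remove the top share p of a normal use propensity that correlates r with the outcome. The mean of those kept shifts by −r·φ(c)/(1−p), where c is the (1−p) quantile. For p = 5%, φ(c)/(1−p) = 0.103/0.95 = 0.109; for p = 15%, 0.233/0.85 = 0.274. The gap of 0.166 gives a spurious difference of 0.05 SD at r = 0.3 and 0.08 SD at r = 0.5. With equal removal it is 0.

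**The case against.** The strongest reply is that the two sections address different periods. The use criterion carries its own limit, T1-T5, which is five consecutive days in an inpatient or day-clinic setting. The relapse and consumption outcomes belong to T6-T9, and the retention paragraph goes on to speak of reimbursement in the follow-up period. Abstinence during treatment and retention after relapse in follow-up is a coherent reading. This stands, and it is why the T1-T5 conflict is conditional.

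Second, the breath criterion concerns alcohol on the day, not relapse as such. Someone who has relapsed but attends sober does not meet it, and all participants are to be contacted or invited at every follow-up. This also stands. It narrows the firm conflict to a positive test at T8 but does not remove it, because that person meets the criterion and is also someone the study says may complete.

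Third, the article does not say whether meeting a criterion stops treatment, cancels a visit, or removes the person or the data, and analysis sets are commonly left to documents not shown. So bias is a consequence of one way of applying the text, not a stated analysis rule. The contradiction between two printed statements does not depend on what those other documents say.

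**Conclusion.** The point holds as a conflict of wording with a conditional statistical consequence. It is firm for the breath criterion at T8 and conditional for use in T1-T5. If the criteria are used to take people out of the study or the analysis, the result is outcome-related selection after randomisation. Its effect would probably be small if few participants are positive on the visit day and removal is similar across arms (0.20 falls to 0.1995 or 0.198 SD in the illustration). It is larger, and can go either way, if removal differs by arm (0.14 to 0.26 SD, or a spurious 0.05 to 0.08 SD with no true effect). The removal rates, the 1 SD gap and the correlations are assumptions; the article gives no figures for them.

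A reader might infer three stronger things that the documents do not support:

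- **That exclusion would wipe out the treatment difference.** This needs every relapser removed, which no rule in the article does, and it assumes that the whole craving effect runs through relapse. The 20-80% relapse range in the Background has no time frame and describes neither a five-day treatment block nor a single visit.
- **That bias always runs towards no difference.** The illustrations above show both directions.
- **That the Cox model loses early events from T1-T5.** Table 1 does tick time to relapse at T1 and T5, but the hypothesis and the Statistical analyses section place the relapse and abstinence outcomes in follow-up, so this depends on a time origin that is not stated.

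**What to change.** Reconcile the Exclusion criteria with the section on risks and strengths:

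1. Separate criteria that decide eligibility before randomisation from rules for events that occur afterwards.
2. State that everyone randomised stays in follow-up and is analysed in the assigned arm, whatever use occurs later.
3. State that craving, Form 90 and relapse data are kept after a positive test.
4. State how that visit's Go/No-Go and EEG data are handled, for example by a re-booked assessment, or as missing for that visit only. In the second case, use an analysis that keeps the participant's other visits, such as a mixed model for repeated measures. A conventional repeated measures ANOVA with listwise deletion would drop the whole T1, T5 and T8 series. Data missing because of drinking are still outcome-related, so report the number affected by arm.
5. Add a sensitivity analysis that excludes affected participants.

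Whether add-on sessions or visits go ahead after use or a positive test is a clinical matter for the sponsor to settle when reconciling the passages; no rule is proposed here. The cost is wording plus one sensitivity analysis.

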### Experimental procedure

*N* = 162 SUD patients, who voluntarily enter a qualified detoxification treatment program, will be examined (inpatient or day-clinic setting) at the Department of Addictive Behaviour and Addiction Medicine at the Central Institute of Mental Health in Mannheim, Germany and the Clinic for Addiction Therapy and Withdrawal at the Psychiatrisches Zentrum Nordbaden in Wiesloch, Germany. A randomized assignment (block randomization with permuted blocks of size 12) to one of six groups will be performed. All participants will be included during their second week of hospital stay to ensure completed detoxification (at least 7 days of abstinence) and enrollment in the treatment as usual (TAU). TAU comprises an at least three weeks long therapy duration including medical and therapeutic treatment. We will follow a placebo-controlled single-blind study design, in which participants do not receive any information about electrode placement or active vs. sham condition, except in the non-tDCS groups, namely group 5 (inhibition training) and group 6 (TAU).

Four groups will receive 20-min tDCS sessions using the Sooma Duo™ device (Sooma Oy, Helsinki, Finland) over five consecutive days at an intensity of 2 mA (≈0.08 mA/cm^2^). Electrodes (25 cm^2^) will be placed using a standardized EEG cap following the 10–20 system to ensure consistent positioning across sessions [44]. The current will be ramped up from 0.3 mA to 2 mA at 0.1 mA/s, maintained for 20 min during active stimulation. Stimulation sites will differ by group:

Group 1: Anode over right DLPFC (electrode position F4), cathode over left DLPFC (electrode position F3)Group 2: Anode over left DLPFC (electrode position F3), cathode over right DLPFC (electrode position F4)Group 3: Anode over occipital cortex (electrode position O1), cathode over electrode position Cz.Group 4 will receive sham stimulation (anode over electrode position F3, cathode over electrode position F4). For blinding, the current will ramp up to 2 mA and then immediately ramp down to 0 mA, mimicking the sensation of active stimulation while avoiding physiological effects. With respect to sham tDCS as a control condition, a strong and possibly heterogonous placebo effect is still under discussion. This effect may also be due to using short, active stimulations at the beginning of a sham tDCS that could induce neurophysiological changes [75]. However, an active sham condition will improve blinding of the participants towards the intervention as switching off the current does not represent a reliable sham [77].Group 5 receives a computerized inhibition training using a go-/no-go-task with individually adapted, alcohol-related stimuli, as described in Stein et al. [13].Group 6 receives only TAU but follows the same study protocol with respect to all measurement timepoints; however, there is no contact from T2 and T4. During the follow-up period of 24 weeks, a total of one personal and three telephone contacts are planned. All participants will be contacted after 4, 8, and 24 weeks via telephone and possible relapses and amount of substances consumed will be assessed in a self-reported manner. For the third follow-up after 12 weeks, all participants will be invited for a personal follow-up assessment (timepoint T8). See Figure 1 for further details.

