#### Follow-up 1 (T6), 2 (T7) and 4 (T9; duration ca. 10 min)

All participants (groups 1 to 6) will be asked to answer questions regarding (possible) relapse and amount of substance consumed using REDCap electronic data capture tools hosted at the Central Institute of Mental Health [97, 98]. Subsequently, they will complete an interview via telephone four, eight and 24 weeks after T5. Relapse and amount of substances consumed will be recorded. Craving will also be assessed. A full list of assessments is provided in Table 1.

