### Statistical analyses

The behavioral and EEG results of the inhibitory control paradigm [78] and craving ratings are defined as primary outcome measures. The results of the inhibitory control paradigm will be compared between testing days before (T1) and after fifth (T5) stimulation or training and after a follow-up period of 12 weeks (T8). Craving rates will be compared before and after the first stimulation/training (T1) and across the subsequent stimulation/training sessions (T2-T5), as well as during the follow-up period (T6-T9). Secondary outcomes include duration of abstinence and amount of substance consumed during the follow-up period.

Regarding the EEG data, resampling (to 250 Hz), filtering (70 Hz high- and 0.1 Hz low-pass filter; 50 Hz notch filter), re-referencing to an average reference, manual inspection, independent component analyses, and segmentation (from –200 to 1200 ms) will be conducted. Removed channels due to technical and regular artifacts (e.g., movement artifacts, excessive noise) will be interpolated using neighboring electrodes. ERP components will be scored as mean amplitudes between 200–300 ms and 300–500 ms over fronto-central and central-parietal electrodes for the N200 and P300 components, respectively. All data (EEG, neuropsychological and psychometric data) will be analyzed using t-tests, repeated measures analysis of variance (rmANOVA) and Pearson correlations. The influence of treatment modality (tDCS add-on intervention over various locations versus inhibition training versus standard treatment) on relapse will be tested with a Cox Regression (outcome variable: time until first relapse). Due to the included individuals and the matched-group design, potential influencing factors on primary and secondary endpoints (e.g., type of substance, severity of SUD, number of comorbidities) will be included in the analyses as covariates. In secondary analyses, we will also take a closer look at the potential influence of these factors on treatment response. In this way, it might be possible to identify subgroups that respond particularly well to the treatment (‘treatment responders’) with the goal of precision-targeted treatments for addiction. Statistical analysis will be conducted using SPSS (IBM Corp., Armonk, N.Y., USA).

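### Participants are the only party described as blinded, and no masking is stated for those who clean the EEG behind the primary N200 and P300 amplitudes

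*Protocol article*

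**What the plan says.** Experimental procedure sets the level of blinding: "We will follow a placebo-controlled single-blind study design, in which participants do not receive any information about electrode placement or active vs. sham condition". Groups 5 (inhibition training) and 6 (treatment as usual) are excepted, so participant blinding covers groups 1 to 4. The reason given for the sham also concerns participants: "an active sham condition will improve blinding of the participants towards the intervention". The article names no other blinded party.

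Statistical analyses fixes what is primary: "The behavioral and EEG results of the inhibitory control paradigm [78] and craving ratings are defined as primary outcome measures". For the EEG it lists resampling and filtering, and then "re-referencing to an average reference, manual inspection, independent component analyses, and segmentation (from –200 to 1200 ms) will be conducted". It adds: "Removed channels due to technical and regular artifacts (e.g., movement artifacts, excessive noise) will be interpolated using neighboring electrodes". The components are then scored as mean amplitudes in fixed windows, 200–300 ms for N200 and 300–500 ms for P300.

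The second primary hypothesis is directional: right DLPFC stimulation is expected to increase both amplitudes at T5 and T8.

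Relapse and consumption are secondary. For T6, T7 and T9 participants answer questions in REDCap, and then: "Subsequently, they will complete an interview via telephone four, eight and 24 weeks after T5". Table 1 names the Form 90 interview as the instrument.

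**The concern.** Fixed windows protect only the last step of the ERP pipeline. The mean amplitude in a window depends on which segments, independent components and channels were kept, and the listed cleaning steps include human judgement. A processor who knows that a file is a T5 recording from group 1, and knows the hypothesis, could make borderline calls differently without intending to. Masking the participant does nothing about this.

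The sham arm is there to separate stimulation from expectation. If knowledge of the arm reaches the cleaning step, expectation can re-enter the ERP contrasts on the staff side. Those contrasts include right against left and right against sham, which the trial was built to test.

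**Working it through.** **Where judgement can enter, outcome by outcome**

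- *N200 and P300 (primary).* Manual inspection, component rejection and channel removal involve judgement; scoring in fixed windows does not. Exposed at the cleaning stage.
- *Go/No-Go behaviour (primary).* Computer-administered and computer-scored. Not exposed by this route.
- *Craving (primary).* Self-rated on questionnaires. Not exposed by this route.
- *Relapse and amount consumed (secondary).* Self-reported, asked in REDCap and recorded by interview with the Form 90. Some interviewer influence is possible. Table 1 also has urine screening at T8, but not at T6, T7 or T9.

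**How many recordings are involved**

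Table 1 places the Go/No-Go EEG at T1, T5 and T8, so up to 162 × 3 = 486 recordings. The Follow-up 3 section calls the T8 recording the second one; on that reading the count is 162 × 2 = 324. Either figure counts exposure and is not evidence of bias.

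**The planned effect as a yardstick**

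The Sample size section gives f = 0.15, 80% power, alpha 5% and 25 per group, for a within-between interaction in a repeated measures ANOVA. The number of measurements m and the correlation ρ are not given. With six groups and assumed m = 2 and ρ = 0.5:

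- λ = f² × N × m / (1 − ρ) = 0.0225 × 150 × 2 / 0.5 = 13.5
- df = (6 − 1)(2 − 1) = 5 and (150 − 6)(2 − 1) = 144
- power = 0.806, so 25 per group is reproduced.

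Masking changes neither N nor alpha. For a rough sense of scale, f can be turned into a standardised difference d by the simple between-group conversion, which depends on the pattern of means:

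| Pattern | Conversion | d | Assumed 0.1 SD bias / d |
|---|---|---|---|
| Two groups only | d = 2f | 0.30 | 0.33 |
| One arm apart from five equal arms | d = f / √(5/36) = 0.15 / 0.373 | 0.40 | 0.25 |
| Two arms at the extremes, four midway | d = f × √12 | 0.52 | 0.19 |

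**What a bias would do, if there were one**

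The bias b is an assumption; no value is given in the documents. For two arms of 27 with a two-sided 5% test and no true effect, the standard error is √(2/27) = 0.272 SD. The false-positive rate is 1 − Φ(1.96 − b/0.272) + Φ(−1.96 − b/0.272):

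- b = 0: 5.0%
- b = 0.1 SD: 6.6%
- b = 0.2 SD: 11.4%
- b = 0.3 SD: 19.7%

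**What coded files could hide**

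Experimental procedure says the tDCS electrodes occupy F3 and F4 in groups 1, 2 and 4, and Cz and O1 in group 3. The missing channels may thus separate groups 1, 2 and 4 from group 3, and both from groups 5 and 6. Within groups 1, 2 and 4 the layout is the same, so a coded file would not show whether stimulation was right, left or sham.

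**The case against.** The strongest reply is that the article never says the EEG staff know the arm. A single-blind label is compatible with an offline pipeline on coded files, and a condensed article may leave such detail to the full protocol. This stands in part: staff knowledge is an inference from the label and from silence about anyone other than participants. But the article does state its level of blinding and gives only participants as masked, so the point concerns a choice it makes.

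A reader might go further and infer that the EEG staff are unmasked as a fact, or that the sham comparison as a whole no longer isolates stimulation. The documents support neither. Two of the three primary components do not pass through manual cleaning, and scoring of the third is rule-based once cleaning is done.

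A reader might also put the relapse data on the same footing. They are secondary, self-reported and taken with a named interview, and nothing in the article describes how interviewers probe. Making the REDCap entry the source of the endpoint would demote the planned Form 90, which is a trade-off and not a plain gain. Changing the interviewer assumes staffing that the article does not describe, and participants in groups 5 and 6 know their condition and could reveal it.

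Finally, a reader might take the bias to be about a third of the planned effect. That needs one assumed bias and a two-group conversion; six-group patterns give 0.19 to 0.25.

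**Conclusion.** The point holds in a limited form. One component of the primary outcome, the N200 and P300 amplitudes, passes through manual steps for which no masking is stated, under a directional hypothesis and a design that describes only participants as blinded. This leaves a route for observer bias in up to 486 recordings. Whether any bias would arise, and how large it would be, cannot be known from the documents; the false-positive figures rest on assumed values. The conclusion also assumes that single-blind carries its usual meaning here and that no coding rule stands in a fuller document. It is a cheap improvement worth making, not a flaw that invalidates the trial.

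**What to change.** Give every EEG file a random code that carries neither arm nor visit before manual inspection and component rejection. Break the code only after the cleaned data are locked. State in the protocol who is masked. If files are already handled this way, one sentence saying so is enough.

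The cost is a file-coding step and the upkeep of a key. Masking remains partial, because of the occupied channels, but it covers right, left and sham stimulation.

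For relapse and consumption, keep the Form 90 interview as planned. Only where existing staffing allows, have it done by someone who did not deliver that participant's sessions. Sample size, visits and tests stay as they are.
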